### Targeted population

2.4.

This study will enroll up to 30,000 patients undergoing clinically indicated CCTA and follow-up for 3–4 years. This number is based on empirical data to provide adequate data to permit subgroup analyses such as for sex, ethnicity and cardiovascular risk factor categories in relation to coronary atherosclerosis. Sites participating in the study will be selected based on data quality and quantity of CCTAs per year, and to achieve adequate representation of race and ethnicity. The study is considered non-significant risk because this is an observational registry with no targeted downstream alteration to the clinical care pathway of the patient or additional interventions. CCTA, in both the US (ACC/AHA) and European guidelines (ESC, NICE guidelines), received a class I indication for the use as a first-line test in chest pain patients.^2,23^

### Eligibility criteria

2.5.

#### Patient eligibility criteria

2.5.1.

Patients referred for clinically indicated CCTA will include those undergoing evaluation for CAD, valvular heart disease or congenital heart disease, and pre-procedural evaluation for CABG, PCI, surgical aortic valve replacement/repair (SAVR), transcatheter aortic valve implantation (TAVI), left atrial appendage (LAA) occlusion, surgical mitral valve replacement/repair (SMVR), transcatheter mitral valve replacement (TMVR), tricuspid valve interventions, patent foramen ovale (PFO) closure, electrophysiological (EP) intervention including pre-pulmonary vein isolation (PVI). All consecutive patients who have presented or are presenting for clinically-indicated CCTA of ≥64-detector rows and who meet all the inclusion criteria and none of the exclusion criteria will be included into CONFIRM2. Further inclusion and exclusion criteria are described in Table 1.

#### Site eligibility criteria

2.5.2.

Each clinical center is required to obtain IRB approval for the protocol and consent (and their revisions) in a timely fashion, to recruit patients, to collect data and enter it accurately in the electronic data capture (EDC) system, to faithfully follow the protocol and adhere to the standards of Good Clinical Practice (GCP). Each participating site contributing patient data to CONFIRM2 fulfills the following site requirements: (1) greater than 500 patients per annum undergoing CCTA by ≥ 64-detector rows, (2) able to perform follow up on recruited patients, (3) able to organize data required for completion of CONFIRM2 case report form, and (4) able to perform de-identification of Protection Health Information (PHI) securely on-site in a manner in keeping with local and international regulations. In addition to site specific IRB evaluation, central IRB approval of CONRIFM2 was obtained.

### Study sites/participating centers

2.6.

Since the recruitment of patients started in 2021, 20 sites have contributed data to the CONFIRM2 from 11 countries (United States, Japan, The Netherlands, Italy, Switzerland, Austria, Saudi Arabia, Israel, Portugal, Brazil, and Germany). The dynamic nature of the study allows further inclusion of sites in the upcoming years. Qualifying patients will be enrolled, or retrospectively included in the study and followed for 3–4 years through follow up visits and/or phone calls. Up to 50 medical centers from US and out of US will participate in the study, with up to 30,000 subjects entered. Each center may not enroll more than 1000 – 3000 subjects. The geographic clusters were selected to represent medical centers of different sizes with different diagnostic capabilities, as well as differences in clinical and demographical patient populations. The medical centers all have incorporated CCTA into their daily clinical practice.

### Patient evaluation and follow-up

2.7.

#### Patient evaluation

2.7.1.

At baseline, clinical, demographical, laboratory, and imaging data will be collected and entered into the case report form. The indication for CCTA includes: CAD evaluation (symptomatic stable; symptomatic acute; asymptomatic [abnormal stress or other], asymptomatic screening), asymptomatic pre-operative evaluation, TAVI, LAA occlusion, TMVR, tricuspid valve interventions, pulmonary vein ablations, electrophysiological evaluation, congenital heart disease, or other. The following laboratory assessment will be collected: serum creatinine, total cholesterol, LDL-C, HDL-C, triglycerides, HbA1C, CRP, Lp(a), Troponin, BNP. Patient demographics include age, sex, ethnicity/race, height, weight, and vital signs. Patient history of CAD includes prior myocardial Infarction (MI), PCI, and CABG. Concomitant medications will be collected: antiplatelet agents, oral anticoagulants, anti-hypertensives, anti-arrhythmics, Hairt failure medications, lipid lowering agents, diabetic agents, smoking cessation agents, anti-depressants, and pulmonary medications. Risk factors include hypertension, dyslipidemia, diabetes, family history, smoking, sedentary lifestyle, peripheral arterial disease, gestational hypertension, gestational diabetes and menopause. Hypertension was defined as a blood pressure of ≥140/90 mmHg or the use of antihypertensive medication. Dyslipidemia was defined as a total cholesterol level of ≥5 mmol/L or treatment with cholesterol-lowering medication. Patients were classified as having diabetes if they were receiving treatment with oral hypoglycemic drugs or insulin. A positive family history of CAD was defined by the presence of CAD in first-degree relatives younger than 55 years in men or 65 years in women. Imaging data (including actual DICOM images) besides the CCTA will be also collected such as a nuclear myocardial perfusion imaging, CMR stress perfusion imaging, invasive coronary angiography, fractional flow reserve (FFR), optical coherence tomography, and intra vascular ultra sound (IVUS).

#### Follow-up

2.7.2.

During periodical follow-up assessment, the post-CCTA medical treatment, other performed imaging tests (nuclear myocardial perfusion imaging, CCTA, invasive coronary angiography, FFR, or IVUS), clinical presentation (symptoms, pre-test likelihood of CAD), laboratory results, medication usage and dose will be collected to enable longitudinal assessment of risk during the study period. The occurrence of study endpoints (as mentioned previously) will be assessed by the sites during follow-up. The participating sites will submit clinical information including baseline and event electrocardiograms, troponin trends, the discharge summary, invasive angiogram images and clinical reports, brain imaging, and neurology consult reports to the core laboratory for adjudication of the primary and secondary endpoint. An independent event adjudication committee will adjudicate events. A flow chart from patient inclusion to follow-up collection is in Fig. 1.

### Acquisition and interpretation of CCTA

2.8.

Imaging is performed with a CT scanner of ≥64 detector rows. Specific imaging parameters are expected to vary for each type of scanner and by site. Nitroglycerin and, under certain circumstances, beta blockers are recommended prior to CT acquisition in line with the standards of the Society of Cardiovascular Computed Tomography Guidelines for image acquisition.^24^ Scanning parameters, including gating, kVp, mA, and collimation are recommended to be optimized to achieve robust image data and maximum image quality whilst avoiding unnecessarily high radiation exposure as guided by the ALARA (“As Low As Reasonably Achievable”) principle, as set by the standards of the Society of Cardiovascular Computed Tomography Guidelines for image acquisition.^24^ Scan parameters should be included for each patient and include scanner model, mA, kVp, and whether a single or dual-energy mode is used. All de-identified CCTA images will be transferred to the Imaging Core Laboratory, located at Cleerly (Denver, CO, US). Automated software will evaluate CCTAs by a standardized approach in a blinded fashion CCTA analysis will be prescribed in a manual of operations. Stenosis variables that will be derived are amongst others luminal or area diameter stenosis, minimal luminal area, or cross sectional information at the slice of maximal stenosis. Coronary plaque variables are amongst others total plaque volume, the compositional subtypes (low density noncalcified plaque, noncalcified plaque, or calcified plaque), or high risk plaque features. Vascular morphology features include lumen volume, vessel volume, and indices about the remodeling of the coronary artery. The information will be derived from individual CT slice basis up to patient level data. An example of arterial quantification is provided in Fig. 2.

### Data management

2.9.

The Sponsor will perform data management activities including documentation of the systems and procedures to be used. All e-case report form (eCRF) data collection will be performed through a secure web portal and all authorized personnel with access to the electronic data capture system must use an electronic signature access method to enter, review, or correct data.

The data will be subjected to consistency and validation checks within the electronic data capture system. Completed eCRF images with the date-and-time stamped electronic audit trail indicating the user, the data entered, and any reason for change (if applicable) will be archived at the Investigator’s site and a backup copy archived with Cleerly Inc.

Primary data collection based on source-documented hospital and/or clinic chart reviews will be performed clearly and accurately by the clinical site personnel trained on the protocol and eCRF completion. eCRF data will be collected for all patients that are registered into the study.

The sponsor will archive and retain all documents pertaining to the study for the time of the study under evaluation, and for lifetime during the post-study phase. The Investigator must obtain permission from the sponsor in writing before destroying or transferring control of any study investigation records.

### Statistical methods

2.10.

The primary analysis of CONFIRM2 will evaluate the prognostic ability of coronary stenosis, atherosclerosis, and vascular morphology information by quantitative assessment in a cohort of symptomatic or asymptomatic patients undergoing CCTA for evaluation of suspected CAD. Cox proportional hazard models will be used to make inference and describe the magnitude of the prognostic value of each predictor using hazard ratios. Kaplan-Meier curves for the entire cohort and stratified by covariate level (e.g. quartiles of total plaque volume) will provide estimates of the risk of events over time and visualization of the magnitude of the effect of covariate on event probability. Additionally, machine learning techniques will be used to generate a multivariable predictive model. The dataset will be split into a training subset and a validation subset. The test subset will be used to build the predictive model, including evaluating the performance of various machine learning models such as random forest. The validation subset will be used to measure the predictive performance of the resulting model, measured as area under the receiver operating curve. Any covariates with more than 15% missing data will be excluded from analysis. Covariates with missing data that is less than or equal to 15% may be imputed using multiple imputation as a sensitivity analysis to evaluate the effect, if any on the cox model and machine learning results. Subjects with incomplete event data will be censored at the last time they were known to be event-free. The risk of type I errors was set at p < 0.05. In order to reduce the chance of type II errors a sample size of 30,0000 pts was chosen based on empirical data in order to permit adequate subgroup analyses while minimizing beta errors.

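### The machine-learning model is validated by one split and one AUC that do not keep sites apart, so the result need not show how the model performs at a new site

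*Protocol article*

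**What the plan says.** The Statistical methods section of the protocol article plans a multivariable machine-learning model alongside the Cox analysis. Validation is described in three sentences:

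- "The dataset will be split into a training subset and a validation subset".
- "The test subset will be used to build the predictive model". Here a third label appears; presumably the training subset is meant.
- "The validation subset will be used to measure the predictive performance of the resulting model, measured as area under the receiver operating curve".

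The section does not say whether patients, sites, countries or calendar periods are split, or in what ratio. No section names an external cohort or a leave-site-out step.

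Other sections describe the sites:

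- Study sites/participating centers: "Up to 50 medical centers from US and out of US will participate in the study, with up to 30,000 subjects entered". So far, "20 sites have contributed data to the CONFIRM2 from 11 countries". Centres were chosen to vary in size and diagnostic capability and to reflect "differences in clinical and demographical patient populations". Patients may enter prospectively or retrospectively.
- Acquisition and interpretation of CCTA: "Specific imaging parameters are expected to vary for each type of scanner and by site". The same section sends all images to one core laboratory for automated, standardised, blinded reading.

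The Introduction states the aim as better risk prediction and more individualised care for people having CCTA. It does not limit this to the participating centres.

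**The concern.** A validation figure answers the question set by its design. A split that shares sites tells us how the model does for further patients at those sites. The stated aim is wider, and the article itself gives reasons why the two may differ: patient mix, diagnostic capability and scan settings all vary by site.

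Flexible learners can use technical or case-mix features as a proxy for the site and hence for its mortality level. The Statistical methods section gives random forest as an example, and the Overall study design section also mentions deep learning and radiomics. That proxy helps in a validation subset drawn from the same sites and has no value at a site the model has not seen.

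At stake is whether the published AUC can support use of the model outside the registry. A second matter is whether predicted risks are right at a new site, which an AUC cannot show.

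**Working it through.** The article states no split ratio, event rate or performance figure, so there is nothing of its own to reproduce.

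**1. Do sites overlap?** Inputs from the article: N = 30,000 and S = 20 (current) or 50 (planned maximum) sites. Assumed: equal site sizes, a random split by patient, and a validation share f of 0.2 to 0.5.

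The chance that at least one site is absent from validation is at most S × (1 − f)^(N/S).

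- 50 sites of 600, f = 0.2: 50 × 0.8^600 = 3.6e-57.
- 20 sites of 1,500, f = 0.2: 20 × 0.8^1500 = 8.6e-145.
- Larger f gives smaller values. With f at or below 0.5, absence from training is no more likely than absence from validation.

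Sites will not be equal in size; the article says "Each center may not enroll more than 1000 – 3000 subjects". Even a site with only 30 patients would be missing from validation with chance 0.8^30 = 0.001. Under a split by patient, overlap is in practice complete.

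**2. What can a wrong site level do at one new site?** Suppose the model adds a constant c to every log-risk at that site. The ranking of its patients is unchanged, so the AUC within the site is unchanged. All predicted risks are shifted, so calibration is wrong. If several new sites are pooled, wrong constants disturb the ranking between sites and the pooled AUC falls as well.

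**3. How large could the gap be?** This cannot be derived from the article. The following simulation is illustrative and all its inputs except N and the numbers of sites are assumed: about 4% baseline risk, five true predictors, 15 technical features that differ by site but have no effect on outcome, a ridge logistic model, a 70/30 split and 40 runs per setting. The site log-odds have standard deviation τ. The site-split AUC is pooled over the held-out sites.

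| Sites | τ | AUC, split by patient | AUC, split by site | Difference | Observed/expected per held-out site (10th–90th percentile) |
|---|---|---|---|---|---|
| 20 | 0 | 0.672 | 0.669 | 0.003 | 0.83–1.23 |
| 20 | 0.3 | 0.683 | 0.658 | 0.025 | 0.67–1.53 |
| 20 | 0.6 | 0.704 | 0.647 | 0.057 | 0.55–2.25 |
| 20 | 1.0 | 0.738 | 0.602 | 0.136 | 0.37–3.29 |
| 50 | 0 | 0.674 | 0.671 | 0.003 | 0.80–1.30 |
| 50 | 0.3 | 0.678 | 0.667 | 0.011 | 0.61–1.48 |
| 50 | 0.6 | 0.685 | 0.652 | 0.033 | 0.44–1.93 |
| 50 | 1.0 | 0.700 | 0.607 | 0.093 | 0.24–3.16 |

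Without differences in site risk there is no material gap. With them, the two designs diverge. Much of the spread in observed/expected reflects the sites' own risk differences, which any model without local recalibration would face. The planned AUC would not reveal that spread.

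**The case against.** **The unit of the split is not stated.** A split by whole sites would fit the sentence as written, and a fuller protocol or analysis plan, not shown here, may define it so. This stands, and it is why the point is conditional. If sites are in fact held out whole, the overlap disappears. What remains is that the article commits to one split and one AUC and does not itself keep sites apart.

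**A patient-level holdout is valid internal validation.** This also stands. The section claims only the performance of the resulting model, not external validity. The gap lies between that figure and the wider aim in the Introduction.

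**Central, automated, blinded reading limits site effects.** It does, particularly for derived plaque and stenosis measures. It does not remove differences in acquisition, case mix or ascertainment.

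Three stronger readings are tempting but not supported:

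- *The AUC will be too favourable.* This needs sites that differ in baseline risk and a model that exploits site-linked features. The article quantifies neither, and with τ = 0 the simulated gap is about zero.
- *The optimism can be computed from a normal risk model.* Assume a within-site SD of log-risk of 0.8 and between-site SDs of 0.2/0.4/0.6. The pooled AUC with known site levels is Φ(√(0.64 + SD²)/√2) = 0.720/0.736/0.760. Set against Φ(0.8/√2) = 0.714, this looks like optimism. But even a model that knew every patient's true risk would give 0.714 within a single site. The excess is ranking between sites, which a single new site cannot lose.
- *One split wastes data and gives a chance result.* Assuming 30% held out and 4% events, there are 30,000 × 0.30 × 0.04 = 360 validation events, and the standard error of an AUC of 0.72 is about 0.015. At this size that is a secondary matter.

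**Conclusion.** The point holds in conditional form. The article fixes a single split and a single AUC without separating sites. If the split is by patient, the validation figure concerns sites already used for training and does not show transport to new ones. That conclusion needs only the overlap bound, not an assumed effect size.

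Whether the AUC would also be inflated depends on heterogeneity that the article expects but does not quantify. In the illustrative simulation the difference was about 0.00 with no site variation in risk, 0.01 to 0.03 at a site SD of 0.3, 0.03 to 0.06 at 0.6 and 0.09 to 0.14 at 1.0. These figures rest on assumed inputs and are not estimates for this registry. They also refer to held-out sites taken together; at one new site a wrong site level shows as miscalibration, not as a lower AUC. The documents do not support saying that the model will perform badly elsewhere, only that the planned figure need not tell us.

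**What to change.** Replace the single split with internal-external cross-validation: leave out one site or one country at a time, train on the rest, and evaluate on the part left out. With 20 sites in 11 countries already contributing, this needs no new data. A simpler alternative is to make the validation subset a set of whole sites.

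In either case:

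- state the unit of the split, and correct the subset labels so that the model is built on the training subset;
- keep variable selection that uses the outcome, and all tuning, inside the training sites;
- report discrimination and calibration both pooled and for each held-out site;
- refit the final model on all data.

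The cost is a change of wording and more computing. The reported performance may be lower and its interval wider. If the unseen plan already holds out whole sites, only the wording of the article and the per-site and calibration reporting need attention.

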## Discussion

3.

The multicenter, international, CONFIRM2 trial will evaluate multidimensional associations between phenotypical manifestations of cardiovascular disease diagnosed by CCTA, serum biomarkers, clinical patient information, clinical presentation and therapy changes over time in relation to outcome.

A unique aspect of this trial is the use of automated software solutions for assessment of coronary plaque, stenosis, vascular morphology and cardiac structures. This allows quantification of coronary atherosclerotic burden, and its compositional subtypes, and can gauge subtle temporal burden changes in patients from serial CT scans. As such, CONFIRM2 will evaluate the value of quantification of coronary atherosclerosis to refine risk stratification and prediction of future events in comparison to current clinical strategies that are mainly aimed at detecting anatomically “obstructive” stenoses.

There has been great interest over the last several decades to identify the “vulnerable plaque”, a precursor for future ACS, which may allow to apply preemptive interventional strategies.^25–28^ Histopathological studies have shown that most myocardial infarctions or sudden coronary death results from thrombotic vessel occlusion with underlying plaque rupture or plaque erosions.^29^ The plaques associated with these culprit lesions have a thin-fibrous cap with an underlying large inflamed necrotic core and have therefore been proposed as high risk plaques. This approach, however, has been unsuccessful to date and instead the concept of assessing the “vulnerable patient” has been advocated.^30,31^ In part, this may be due to the dynamism of atherosclerotic plaques and the morphologic changes over time that contribute to heightening or lowering the likelihood of any given plaque to destabilize and become culprit lesion.^31,32^

Despite the observations that most vulnerable plaques will not result in clinically apparent coronary syndromes, quantification of high-risk plaque provides incremental information in relation to the overall atherosclerotic burden. The ICONIC study (Incident COroNary syndromes Identified by Computed Tomography), a nested case-control study investigating the prognostic value of these plaques accounting for the denominator of total atherosclerotic burden using a matched population, observed high-risk plaque features such as low-attenuation plaque, positive remodeling, spotty calcifications to independently predict ACS beyond clinical risk factors and total atherosclerotic burden.^18^ Furthermore, in the SCOT-HEART study (Scottish Computed Tomography of the HEART) the burden of low-attenuation plaque was the strongest predictor of MI and cardiac death, beyond calcium score and maximal stenosis in the coronary tree.^19^ These findings stress the need for whole heart atherosclerosis imaging focused on plaque morphology and burden, rather than on stenosis evaluation alone. Identification of high-risk patients, who have not yet experienced a coronary event, helps to allocate resources to potentially prevent the significant mortality and morbidity associated with coronary artery disease. A focus on plaque burden alone, or calcified plaque burden as done with calcium score imaging, provides good prognostic value but is insufficient. Plaque burden and especially the calcified component of plaque increase strongly with age, and do not adequately respond to disease modifying interventions such as diet change, life style modification and statin use.^33–36^

Current lipid lowering therapies halt plaque progression and provoke morphological changes towards lower risk namely an increase in calcified plaque phenotypes (and a regression of non-calcified plaque).^37,38^ Also, regular-moderate to high-intensity exercise of >150 min/week or healthy diets have been associated with plaque changes.^39^ CONFIRM2 will provide detailed quantification of plaque on a patient, lesion, and voxel-level detail from the entire coronary tree using an AI-derived quantitative methodology. We aim to further understand the levels of risk for specific phenotypical manifestations of coronary artery disease, by focusing on plaque type and vessel morphology. We will further explore dynamic associations between medication usage and changes over time, serum biomarkers, and quantified atherosclerosis. This will allow us to identify patients at high-risk who benefit more from imposing early and more specific preventive interventions (e.g. lower LDL-c targets).^39^ Beyond assessment of atherosclerosis, CCTA also enables non-invasive whole heart quantification of extra-coronary manifestations of cardiovascular disease such as left ventricular dilatation, ventricular hypertrophy and scar tissue. Also, associations of structural disease assessment with non-coronary related outcomes such as stroke or heart failure will be explored. This comprehensive analysis of patient specific parameters of vulnerability will assist in advancing precise and personalized medicine.

